### Data collection

Data on demographics (sex, age, ethnicity, education level), lifestyle (smoking, alcohol drinking, salt, physical activity), medical history, use of antihypertensive medication and concomitant drugs (hypoglycemic drugs, lipid-lowering drugs, antiplatelet drugs and anticoagulant drugs, etc.; name, dose, adherence, cost), cognitive status, atherosclerosis examination (PWV, ABI), and laboratory tests will be obtained by trained researchers through standardized questionnaires and measurement (Table 1). Two visits—at baseline and at 12-month termination—will be conducted to obtain repeated BP measurements. Current smoking is defined as smoking at least one cigarette per day and lasting for at least one year. Current drinking is defined as ≥ 2 drinks/week and lasting for at least six months. Physical activity is defined as > 30 min/day of moderate physical activity. The patients will be asked whether they exercise > 30 min per day. If the answer is yes, they will be asked what kind of physical activity they do (running, swimming, fitness, fast walking, cycling, etc.) and the average days per week. Salt and cooking oil are defined as the average salt in home in the past year (g/month).

**Table 1 Tab1:** Data collection schedule

Items	Baseline 1	Baseline 2	Follow-up time (months)				
			1	3	6	12(1)	12(2)
Informed consent	×						
Inclusion and exclusion process	×	×					
Physical examination	×		×	×	×	×	
Lifestyle	×		×	×	×	×	
History of disease	×						
Cognitive status	×						×
Blood pressure	×	×	×	×	×	×	×
Medications use	×		×	×	×	×	
Blood and urine examination		×					×
Atherosclerosis tests		×					×
Incident CVD events			×	×	×	×	

Baseline 1 and Baseline 2 represent the first and second day of the baseline survey, respectively

12 (1) and 12 (2) represents the first and second day of follow-up months 12

*CVD* cardiovascular disease

Each of the BP measurements will be obtained by study nurses who are masked to clinic assignment and measurement will be according to the standard protocol recommended by the American Heart Association [19]. BP will be measured with the participant in a seated position after 5 min of quiet rest. Additionally, participants will be advised to avoid alcohol, cigarettes, coffee/tea, and exercise for at least 30 min before their BP measurement. At the same time, the condition of antihypertensive medications will also be asked before measurement. BP is measured three times on one day with a 1-min interval and the mean of six BP values was calculated and used for all subsequent analysis. BP was measured using a standardized automatic electronic sphygmomanometer (HEM-8102A; Omron, Tokyo, Japan) and one of four cuff sizes (pediatric, regular adult, large, or thigh) will be chosen on the basis of each participant’s arm circumference.

Anthropometric measurements were measured with participants wearing light clothing and without shoes by investigators using a standard protocol. Three measurements will be obtained at each visit for weight, height, waist circumference, and hip circumference; the arithmetic means will be used for analyses.

### Data management and quality control

All individuals in the study cohort will be uniquely encoded according to uniform rules. The data from the epidemiological questionnaire and clinic examination will be reviewed by the quality control specialist. All the investigators will receive training before the trial begins and all the measurements will be obtained using standard methods. All records will be stored securely and confidentially according to standard guidelines. A reason must be indicated when data are altered and all alterations will be saved. To improve response rates, all participants will receive a participation bonus of RMB 100 per person at baseline and a transportation subsidy of RMB 50 per follow-up.

### Safety monitoring and assessment

The researchers will ask patients to report adverse events and the patient’s BP will be continuously monitored. If participants are monitored for excessive BP reduction, the study coordinator will contact the participant to inquire about their health status. This part will be evaluated by specialists in cardiology.

### Data analysis and statistical power

Baseline characteristics (demographics, lifestyle factors, BP, laboratory measurements, and history of disease) will be compared between the intervention and control groups using the independent sample t-test or χ^2^ tests. The mixed-effects model will be used to compare the primary outcome that there is a greater reduction in BP in the intervention group than in the control group. In this model, participants and clinics will be assumed to be random effects and intervention group, time, and the interaction will be assumed to be estimable fixed effects. Logistic regression will be used to analyze the categorical variables. As the measurement of the participants will be carried out at multiple time points, the generalized estimating equation (GEE) will be used for analysis. The proportion of each variable in promoting the generation of outcome will be used for the mediation analysis.

The proposed trial is designed to provide 90% statistical power to detect a ≥ 7.0 mmHg reduction in SBP at the end of the trial, a significance level of 0.05 using a two-sided test and standard deviation (SD) of 20.0 mmHg [20].

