## Methods

### Research design

This study is a multicenter RCT. A total of 400 hypertensive patients from six cities in the Liaoning and Shanxi provinces of China will be recruited. Of these, 200 participants will be assigned to the intervention group and 200 participants to the control group by block randomization. The financial incentives will last for 12 months (Fig. 1). The primary outcome is the net change in SBP from baseline to month 12 between the intervention and control groups. We will also conduct health economic analysis and consider promoting it on a larger scale if meets the cost-effectiveness principle.

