### Randomization and blinding

Patients will be block-randomized to the intervention and control groups in a 1:1 ratio by an independent statistician using a computer-generated randomization list. The randomization will take place after the patients have been enrolled. The randomization is stratified by geographic regions and the number of stratification is 6. Due to the behavioral nature of the intervention, patients and principle investigators will not be blinded to patient allocation. However, investigators responsible for BP measurement and statistics will be masked to clinic assignment. The details of the randomization will be kept confidential until completion of data analysis.

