### Study outcomes

The primary outcome is net change in SBP, defined as the difference between the intervention and control groups from baseline to follow-up months 12. Secondary outcomes include net change in DBP, the proportion of hypertension control (BP < 140/90 mmHg), changes in self-reported medication adherence, body mass index (BMI), physical activity, counselling frequency, counselling content, number of steps in WeChat, pulse wave velocity (PWV), ankle brachial index (ABI), and cost-effectiveness among all participants.

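### The primary mixed model carries clinic only as an unspecified random effect; read as an intercept it cancels from the SBP change contrast, so the six randomisation strata do no work there and the standard error may be slightly too wide

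*Protocol article*

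**What the plan says.** All places are in the Methods of the protocol article.

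- **Randomisation and blinding:** "Patients will be block-randomized to the intervention and control groups in a 1:1 ratio", and "The randomization is stratified by geographic regions and the number of stratification is 6". Study population names six hospitals in six cities, so strata and clinics appear to coincide.
- **Study outcomes** defines the endpoint in these words: "The primary outcome is net change in SBP, defined as the difference between the intervention and control groups from baseline to follow-up months 12". So what is compared is a difference in change.
- **Data analysis and statistical power:** for the primary mixed model the article states that "participants and clinics will be assumed to be random effects". On the fixed part, it adds that "intervention group, time, and the interaction will be assumed to be estimable fixed effects". The form of the clinic effect is not given, and a clinic-by-time term is neither named nor excluded.
- **Same section, categorical outcomes:** "Logistic regression will be used to analyze the categorical variables", followed by a sentence that applies GEE to the repeated measurements. No clinic term is mentioned for these models.

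**The concern.** Stratifying the randomisation balances the arms within each clinic, so clinic differences do not add to the true uncertainty of the treatment comparison. The analysis gains from this only if the model removes those differences from the error term, in a form that acts on the quantity being compared.

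Here that quantity is change in SBP. A clinic random intercept moves every visit of a clinic by the same amount and drops out of change. What would matter is whether clinics differ in how far SBP falls. This is plausible: entry requires raised BP, so regression to the mean is expected, and antihypertensive drug use is recorded but not standardised across the six hospitals. Without a clinic-by-time term, such differences stay in the residual.

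At stake is a slightly wide confidence interval, a test that runs a little below its nominal level, and a small loss of power.

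**Working it through.** **1. The plan's own figure.** Inputs: 7.0 mmHg, SD 20, two-sided 5%, 90% power.

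- n per arm = 2 × (1.960 + 1.282)² × 20² / 7² = 171.5, so 172 per arm and 344 in total.
- With 200 per arm, SE = 20 × √(2/200) = 2.000 and power = 93.8%.
- 400 corresponds to 344 / (1 − 0.14), that is, an unstated loss of about 14%. This does not bear on the present point; it only shows how much slack the design has.

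**2. Does a clinic intercept cancel?** Generalised least squares with known variances; 72 patients in 6 clinics, 36 per arm, balanced within clinic; two visits; participant variance 144, residual variance 200.

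- With complete data, the SE of the group-by-time contrast is 4.714 for clinic intercept variance 0, 36 and 225 alike. This equals √(2 × 200 × 2/36).
- Adding a clinic-by-time variance of 20 leaves it at 4.714. Real clinic differences in change therefore add nothing to the true uncertainty when arms are balanced within clinic.
- With 14% missing at follow-up, it moves from 5.037 to 5.040 as the intercept variance goes from 0 to 225, less than 0.1%.

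So a clinic intercept does essentially nothing for the primary contrast.

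**3. What if clinics differ in change and the model ignores it?** Assumptions, none of them in the documents: six equal clinics of 66 (396 patients, 33 per arm in each); SD of change within clinic 20 mmHg (the article gives an SD of 20.0 but does not say whether it is of change); between-clinic SD of change s; baseline-to-month-12 change only.

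- Correct SE = 20 × √(2/198) = 2.010.
- Reported SE ÷ correct SE ≈ √(1 + (5/6) s²/400). The factor 5/6 arises because six clinic means vary around their own average.

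| s (mmHg) | Formula | SE overstatement | Type I error, simulated | Power at 7 mmHg by formula: ignoring vs modelling clinic change |
|---|---|---|---|---|
| 0 | √1 | 0% | about 5% | 93.6% vs 93.6% |
| 3 | √1.0188 | 0.9% | about 4.9% | 93.4% vs 93.6% |
| 5 | √1.0521 | 2.6% | about 4.5% | 93.0% vs 93.6% |
| 8 | √1.1333 | 6.4% simulated (6.5% by formula) | about 4.1% | 91.9% vs 93.6% |

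Power = Φ(7/2.010 − 1.96 × k), with k the SE ratio for the model that ignores clinic change and k = 1 for the model that includes it. Type I error by formula, 2 × [1 − Φ(1.96 × k)], is 4.8%, 4.4% and 3.7% for s = 3, 5 and 8. A repeat simulation of 20,000 trials per setting gave 4.5%, 4.4% and 3.9%, so these figures are good to a few tenths of a point. Simulated power losses at 7 mmHg run from about 0.2 to 1.8 points.

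**4. Cross-check on another scale.** Hold the total SD of change at 20, take 200 per arm, and let ρ be the share of the variance of change lying between clinics. The SE with clinic change modelled is 2.000 × √(1 − (5/6)ρ).

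- ρ = 0, 0.02, 0.05, 0.10 gives SE 2.000, 1.983, 1.958, 1.915.
- The overstatement is 0%, 0.8%, 2.2%, 4.5%.
- Power rises from 93.8% to at most 95.5%, a gain of 0 to 1.7 points.

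Both scales give the same order of magnitude.

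**5. Hypertension control.** On the risk-difference scale, the SE ratio from ignoring clinic is about 1/√(1 − var(clinic rates)/0.25). For six evenly spaced control rates spanning 40–60%, 30–70% or 20–80%, the variances are 0.0047, 0.0187 and 0.0420, so the SE is about 1%, 4% or 10% too wide. These spans are assumed, and the last is extreme.

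**The case against.** The strongest objection is that the premise is not in the text. The article says that clinics are random effects; it does not say that the effect is an intercept, nor that nothing else is included. A condensed article may leave the exact random-effects structure to the full protocol or SAP, and the plan does bring the clinic into its primary model. This stands as a limit on the claim: the intercept is the usual reading, not a stated fact.

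A reader might infer that the primary standard error is overstated. The documents do not support that. It requires clinics to differ in mean SBP change, and no between-clinic variance is given for level or for change. If there is no such difference, the standard error is correct.

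A reader might also infer that the primary test is invalid or the trial underpowered. Neither follows. The estimate is unchanged, type I error stays at or below 5%, and even at a between-clinic SD of 8 mmHg power at 7 mmHg stays above the planned 90% with 396 patients analysed.

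The missing clinic term in the logistic and GEE sentences is weaker still. Covariates for a secondary outcome are ordinary SAP content.

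What survives is that the one primary model the article describes, read in the ordinary way, uses the stratification factor in a form that cannot help the primary contrast.

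**Conclusion.** The point holds in a limited form. Randomisation is stratified by six regions, while the primary model carries clinic only as a random effect of unstated form, with no clinic-by-time term named. If it is an intercept, the strata remove no error from the change contrast; this part is exact with complete data and holds to within 0.1% in the check with 14% missing. If clinics also differ in mean change, the SE is too wide by about 0.9% to 6.4% for an assumed between-clinic SD of 3 to 8 mmHg, and type I error falls to between about 4.9% and 4.1%. The cost in power at the design effect is at most about 1.8 points.

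These sizes rest on an assumed within-clinic SD of change of 20 mmHg, equal clinics and strata that coincide with clinics. The error is conservative and causes no bias. It is a low-cost improvement to the primary model, not a threat to its validity.

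**What to change.** State the form of the clinic effect, and make it act on change. Either of these does so:

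- in the mixed model, replace the clinic random effect by a six-level clinic factor with clinic-by-time terms; or
- analyse month-12 SBP adjusted for baseline SBP and the six-level clinic factor, where the clinic main effect is enough.

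As a lesser point, include the six-level clinic factor in the logistic/GEE model for hypertension control. The precision figures above apply to a risk difference; a clinic-adjusted odds ratio is a different quantity from an unadjusted one, so the effect measure should be named.

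The cost is a line of wording and about 5 degrees of freedom per visit; in the month-12 change analysis, 389 remain (396 − 7). Where clinics do not differ, simulated power at 7 mmHg was the same with and without the clinic factor (93.4% in both, to one decimal). The change should be fixed before allocation is revealed to the analysts.

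### The stated primary model does not adjust for baseline SBP; adjusting would sharpen the month-12 contrast at no cost, and the SD of 20 mmHg should be labelled

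*Protocol article*

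**What the plan says.** Under Study outcomes, the protocol article defines the primary outcome as the difference between arms in SBP change from baseline to month 12. Under Data analysis and statistical power it names a mixed-effects model with participants and clinics as random effects, in which "intervention group, time, and the interaction will be assumed to be estimable fixed effects". It lists no baseline covariate and states no constraint that the arms share a baseline mean. In that section, baseline BP appears only among the characteristics to be compared between arms.

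On power, the same section says: "The proposed trial is designed to provide 90% statistical power" for a difference of at least "7.0 mmHg reduction in SBP at the end of the trial", with "a significance level of 0.05 using a two-sided test and standard deviation (SD) of 20.0 mmHg". It does not say whether this is the SD of SBP at one visit or of its change. Research design gives the size: "200 participants will be assigned to the intervention group and 200 participants to the control group by block randomization".

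Table 1 schedules BP on two baseline days, at months 1, 3 and 6, and on two days at month 12. The measurement text takes three readings a day and analyses the mean of six.

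**The concern.** A model with free group, time and interaction effects lets the arms have different true baseline means, although randomisation makes those means equal in expectation. If baseline is one of the outcome occasions, the month-12 interaction subtracts the whole observed baseline difference. SBP at month 12 is imperfectly correlated with SBP at baseline, so part of what is subtracted is noise. An analysis that lets the data set the weight on baseline does at least as well in large samples and normally better.

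The primary confidence interval would therefore be wider than it need be. The choice also interacts with the unlabelled SD: the power of an unadjusted change contrast depends on the SD of change, and the reader cannot tell whether 20 mmHg is that quantity.

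**Working it through.** **Inputs from the article.** Difference 7 mmHg; SD 20 mmHg; two-sided alpha 0.05; target power 90%; 200 per arm. **Assumed:** the correlation r between baseline and month-12 SBP, which the article does not give, shown over a range.

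**1. The article's own figure.** n per arm = 2 × (1.960 + 1.2816)² × 20² / 7² = 171.5, so 172 per arm (344 in all). At 200 per arm the standard error is 20 × √(2/200) = 2.0, and power is Φ(7/2.0 − 1.960) = Φ(1.54) = 93.8%. So 400 patients exceed the stated 90% if 20 is the SD of the quantity analysed. The 28 spare patients per arm would cover 28/200 = 14% loss; the article states no attrition allowance.

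**2. What the stated model estimates.** With baseline as a time level, categorical time, a participant intercept and complete data, the month-12 interaction equals (mean change, intervention) − (mean change, control).

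**3. Variance of the two contrasts.** Let s0 and s12 be the baseline and month-12 SDs. Per patient:
- change score: s12² + s0² − 2·r·s0·s12
- baseline-adjusted: s12²·(1 − r²)
- difference: (s0 − r·s12)², which is never negative.

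With s0 = s12, adjusted over change is (1+r)/2: 0.65, 0.75 and 0.85 at r = 0.3, 0.5 and 0.7.

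**4. Effect of the entry criterion.** Requiring 140/90 mmHg or above at two visits narrows s0. Take s12 = 20 and r = 0.3 for illustration, so the adjusted variance is 400 × 0.91 = 364:

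| s0 (assumed) | Change variance | Change SD | Saving from adjustment | Power of change score, 200 per arm |
|---|---|---|---|---|
| 10 | 380 | 19.5 | 4% | 94.9% |
| 12 | 400 | 20.0 | 9% | 93.8% |
| 15 | 445 | 21.1 | 18% | 91.3% |

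Simulated truncation agrees: savings of about 3–10% when SBP is at least 140 on both baseline days, and about 7–23% when one reading is truncated at 140 (assumed pre-selection mean 135–155, SD 20, r 0.3–0.6).

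**5. Power under the two meanings of SD 20, equal variances, 200 per arm.** If 20 is the single-visit SD, the SD of change is 20√(2(1−r)) and the adjusted SD is 20√(1−r²):

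| r (assumed) | Change SD | Power, change | Adjusted SD | Power, adjusted |
|---|---|---|---|---|
| 0.2 | 25.3 | 79.0% | 19.6 | 94.7% |
| 0.3 | 23.7 | 84.1% | 19.1 | 95.6% |
| 0.4 | 21.9 | 89.2% | 18.3 | 96.8% |
| 0.5 | 20.0 | 93.8% | 17.3 | 98.1% |
| 0.6 | 17.9 | 97.5% | 16.0 | 99.2% |
| 0.7 | 15.5 | 99.5% | 14.3 | 99.8% |

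The largest SD that still gives 90% is 7 / (√(2/200) × 3.2416) = 21.6 mmHg. Setting 20√(2(1−r)) = 21.6 gives r = 1 − (21.6/20)²/2 ≈ 0.42.

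If 20 is the SD of change, the unadjusted contrast has 93.8% power, and adjustment raises it to 99.1%, 98.1% or 96.7% at r = 0.3, 0.5 or 0.7.

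**The case against.** The article does not say that baseline is an outcome occasion, that time is categorical, or that its list of terms is complete. A full protocol or analysis plan, not shown here, might add baseline SBP. That stands, and the point rests on the natural reading, not on an explicit statement. The article does, however, set out the fixed and random effects of the primary model, so improving them is comment on a stated method and not a complaint about missing detail.

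A reader might infer three stronger things that the documents do not support.

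- *That 90% power is not reached.* The article's inputs give 93.8%. A shortfall at 200 per arm needs 20 to be a single-visit SD, near-equal variances and r below about 0.42, or else losses above about 14%. None of these is stated. Selection also works against it: the 84.1% at r = 0.3 becomes 91.3–94.9% for baseline SDs of 10–15.
- *That regression to the mean biases the comparison.* Selection on high BP makes it expected, but it acts on both randomised arms and cancels in expectation. Only conditional on an observed chance imbalance does the change score over-correct. That is a matter of precision.
- *That adjustment saves 15–35% of the variance.* Those values come from (1+r)/2 at r = 0.7 to 0.3 with equal variances, which does not suit a population selected at 140/90 mmHg or above.

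Site is also already handled by the clinic effect. Randomisation is stratified ("The randomization is stratified by geographic regions and the number of stratification is 6"), and six institutions in six cities are listed, so fixed rather than random site terms would be a preference.

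**Conclusion.** A free improvement, not a validity failure. On the natural reading, the stated primary model gives an unadjusted difference in mean change: unbiased under randomisation, but less precise than a baseline-adjusted contrast. With equal variances the variance ratio is (1+r)/2. For this selected population the saving is probably smaller, roughly 3 to 20%, and its size depends on assumed truncation and correlation. In large samples it cannot be negative.

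The stated power is not contradicted. It cannot be confirmed for the unadjusted contrast because the SD is unlabelled: 93.8% if 20 is the SD of change, and below 90% at 200 per arm only if 20 is the single-visit SD with equal variances and r under about 0.42. In every equal-variance case tabulated, the adjusted analysis stays above 90% at 200 per arm, so adjustment also makes the ambiguity matter less.

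**What to change.** 1. Make the primary analysis a longitudinal model of SBP at months 1, 3, 6 and 12, with baseline SBP (the mean of six readings) as a covariate interacting with time, group by categorical time, and the stated clinic effect kept. A model that keeps baseline as an outcome but imposes a common baseline mean is an equivalent route, provided the covariance between baseline and later visits is left free.
2. Name the month-12 group contrast as the primary test.
3. Use the same form for DBP.
4. State whether the SD of 20 mmHg is that of SBP at one visit or of its change.

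The cost is a few sentences in the analysis section. Every variable is already scheduled in Table 1; no patients, visits or measurements are added.
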